### Data management and quality assurance

In this study, electronic CRFs (eCRFs) are used to collect data, and the EDC system designated by the principal investigator is used to complete the eCRF. Monitors verify the original data to ensure that the data entered into the eCRF by authorised trial centre personnel (ie, original data) are accurate, complete and derived from original documents. Researchers and trial institutions must provide monitors with direct access to applicable source documents and reports for inspection and Independent Ethics Board/Ethics Committe review (see online supplemental file 14 for details). A Data Safety Committee has also been established, consisting of five members who are independent of the project team and have signed a research confidentiality agreement. The main tasks of the committee are to review and analyse positive results (recurrence and metastasis of subjects) and to understand the actual research results (without statistical analysis) when half of the subjects are enrolled. The committee will vote on whether it is necessary to adjust the research plan. This protocol does not include investigational drugs, and any toxicities that occur during treatment should be reported to the principal investigator and their Ethics Committee. In addition, the subcentres should also report to the Ethics Committee of their institution. All SAEs and other AEs must be recorded in the CRF. Furthermore, we have established a comprehensive quality control standard operating procedure, as detailed in online supplemental file 15.

### Sample size estimation

This study is designed for superiority, referring to authoritative postoperative radiotherapy studies MA20^10^ and EORTC 22922^11^ for N1 patients, in which the 5-year IDFS in the radiotherapy group and the control group was 90.7% vs 81.9% and 87.7% vs 77.1%, respectively. In the domestic RecurIndex external validation retrospective study^21^ for patients with N1 breast cancer, the 5-year IDFS in the high RecurIndex-LRR risk group was 81.1% vs 69.7% in the postoperative radiotherapy group and the control group, respectively. It is expected that the 5-year IDFS for the clinically low LRR risk and high RecurIndex-LRR risk population in the experimental group and control group in this study will be 89% and 82%, respectively. The superiority margin is set to improve the primary endpoint IDFS by ≥7% (HR=0.587) in the postoperative radiotherapy research group compared with the control group. With a one-sided significance level (α) of 0.025 and a power (1–β) of 0.8, assuming the experimental group performs better than the control group, the required sample size for each group was calculated as 216 cases per group using PASS V.15.0 software. The allocation ratio between the experimental and control groups was set at 1:1. Considering a 5-year enrolment period, 5-year follow-up period and potential 20% dropout rate (mainly considering the need for further 10-year and 15-year long-term efficacy follow-up after reaching the 5-year endpoint), each group will need 270 cases, totalling 540 cases.

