### Participants and recruitment

Patients will be recruited by radiation oncologists from each participating research centre. For each interested patient, the clinician or clinical coordinator will provide a complete and comprehensive introduction to them or their designated representative, informing the patient about their rights, the risks involved and the potential benefits they may receive to enhance their compliance with the protocol. Prior to enrolment, patients are required to sign an informed consent form, which will be kept in the case report form (CRF). Patient registration is scheduled to begin on 1 April 2023 (see online supplemental file 1 for details), and is expected to continue for 5 years (tentatively until January 2028). The final collection of data for the primary outcome measures is anticipated to be completed by December 2032.

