### Statistical analysis

Descriptive statistical analyses will be conducted based on demographic characteristics such as age, gender, height, weight and other baseline characteristics such as medical history. The Cox proportional hazards model will be used for analysis of the primary endpoint. The HR and its 95% CI will be calculated, including stratification factors and other covariates. Additionally, the Cox proportional hazards model without covariates will be used to support the analysis results of the primary endpoint. Moreover, the Kaplan-Meier (KM) method will be used to calculate the median IDFS for the two groups (experimental group vs control group), including 95% CIs. KM plots will be used to illustrate the time trends of IDFS. For the secondary endpoints, the AFR of each group will be calculated, as well as the corresponding 95% Clopper-Pearson CIs. LRFS, DMFS, RFS, OS, DFS and BCSM will be analysed for median values using the KM method (including 95% CIs). The overall changes in EORTC QLQ-C30 and EORTC QLQ-BS23 scores from baseline will be summarised. Safety analysis will be conducted by summarising AEs, changes in laboratory test results, changes in vital signs and study treatment exposure. The results will be reported by treatment group. All AEs during treatment, grade 3 or higher treatment-emergent AEs (TEAEs), SAEs, radiotherapy-related SAEs and TEAEs leading to study termination will be summarised by organ system, preferred term, and group in terms of numbers and percentages (see online supplemental file 16 for details). A p value of ≤0.05 in a two-tailed test will be considered statistically significant. Statistical analyses will be performed using SPSS V.25.0 and STATA V.14.

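### The stated design inputs do not give 216 per group for 80% power: they need about 266–279 evaluable patients per group, and 216 gives about 70% power

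*Protocol article*

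**What the plan says.** The Sample size estimation section expects 5-year IDFS "in the experimental group and control group in this study will be 89% and 82%, respectively", which it expresses as HR 0.587. The calculation is made "With a one-sided significance level (α) of 0.025 and a power (1–β) of 0.8", and it reports that "the required sample size for each group was calculated as 216 cases per group using PASS V.15.0 software". On allocation: "The allocation ratio between the experimental and control groups was set at 1:1". The step from 216 to 270 per group (540 in total) is justified by "Considering a 5-year enrolment period, 5-year follow-up period and potential 20% dropout rate"; the same sentence adds that the dropout figure mainly reflects later 10- and 15-year follow-up.

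The Statistical analysis section names a Cox model for the primary endpoint and says: "A p value of ≤0.05 in a two-tailed test will be considered statistically significant". Under Participants and recruitment, enrolment runs from April 2023 tentatively to January 2028, and "The final collection of data for the primary outcome measures is anticipated to be completed by December 2032". The follow-up section places the end-of-study visit 60 months after the last participant completes radiotherapy. Individual follow-up is therefore about 5 to 10 years. The article does not name the PASS procedure.

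**The concern.** The primary analysis is time-to-event, so its power depends on the number of IDFS events. With control IDFS of 82% at 5 years, events are infrequent, and a total of 432 patients followed for 5 to 10 years looks too few for a hazard ratio of 0.587 at one-sided 0.025. Alpha is not in doubt as written, because two-sided 0.05 in the analysis section equals one-sided 0.025 in the sample size section.

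If 216 is too small for the stated inputs, the trial is described as having 80% power plus a dropout reserve when part or all of that reserve is needed to reach 80% at all. A non-significant result could then be read as stronger evidence against regional nodal irradiation than the design supports.

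**Working it through.** **Inputs** (Sample size estimation): IDFS at 5 years 0.89 and 0.82; one-sided alpha 0.025; power 0.80; 1:1 allocation; 5 years' entry plus 5 years' further follow-up. **Assumed, not stated:** exponential IDFS, uniform entry.

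**Hazards.** Control: −ln(0.82)/5 = 0.03969 per year. Experimental: −ln(0.89)/5 = 0.02331. Ratio 0.5872, which agrees with the stated 0.587.

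**Required events.** (1.960 + 0.8416)² = 7.849.
- Schoenfeld: 4 × 7.849 / (ln 0.5872)² = 31.396 / 0.2834 = 110.8.
- Freedman: 7.849 × (1.5872/0.4128)² = 116.0.

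**Event probability** with 5+5 years: 1 − [exp(−5λ) − exp(−10λ)]/(5λ). This gives 0.2562 (control) and 0.1599 (experimental), mean 0.2081.

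**Required number.** Per group: 110.8/0.2081/2 = 266 (Schoenfeld) and 116.0/0.2081/2 = 279 (Freedman). A Lakatos-type log-rank calculation gives 275. The stated 216 is not reproduced.

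**Power at 216 per group.** Events: 432 × 0.2081 = 89.9. Schoenfeld: Φ(√89.9/2 × 0.5324 − 1.960) = Φ(0.564) = 71%. Freedman gives 69%, Lakatos 70.0%, and 10,000 simulated log-rank trials 70.3%.

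**Attempts to recover 216:**

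| Variant | n per group | Conflict with the text |
|---|---|---|
| One-sided 0.05, 5+5 years | 210 Schoenfeld, 217 Lakatos, 220 Freedman | stated alpha |
| One-sided 0.025, ten full years for every patient | 207 Schoenfeld, 213 Lakatos, 217 Freedman | staggered entry with an end about 5 years after the last patient |
| One-sided 0.025, exactly 5 years each | 382 Schoenfeld, 400 Freedman | does not give 216 |
| Two proportions at 5 years | 396 (425 with continuity correction) | does not give 216 |

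The inflation itself is correct: 216/0.8 = 270.

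**Power for the 540 to be enrolled** (Schoenfeld, 5+5 years; dropout at a constant rate is an assumption):

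| Dropout | Expected events | Power |
|---|---|---|
| None | 112.4 | 80.6% |
| 20% over 15 years | 106.4 | 78.4% |
| 20% over 10 years | 103.6 | 77.3% |
| 20% over 7.5 years | 100.9 | 76.2% |
| 20% over 5 years | 95.8 | 74.1% |

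Freedman's form gives about 2 points less in each row.

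**Sensitivity of the result at 216 per group** (Schoenfeld):
- Entry rate falling linearly to zero: 75%. Entry rate rising linearly from zero: 67%.
- The article's own calendar (April 2023, January 2028, December 2032): 88 events, about 70%.
- Weibull IDFS through the same 5-year rates: shape 0.8, 68%; shape 1.2, 74%; shape 1.5, 79%.

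**The case against.** Four points can be made in the plan's defence.

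**The trial enrols 540, not 432.** A reader might infer that the planned trial has only 71% power. That does not follow. Patients who drop out contribute time and events until they leave, and with no loss 540 patients give about 80%. The article also ties the 20% mainly to long-term follow-up after the 5-year endpoint, which favours the milder rows of the dropout table. This stands: for the enrolled trial the shortfall is roughly 2 to 6 points. It does not rescue the 216, which is presented as sufficient before any dropout.

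**The cause is unknown.** It is tempting to say that 216 arises only if everyone is followed for ten years. One-sided alpha 0.05 with the stated 5+5 years reproduces it about as well, and the article does not show the software inputs. The cause must be left open. Either way, an input used differs from an input stated.

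**The power figures are conditional.** The article states neither exponential IDFS nor uniform entry. This also stands, and about 70% should not be called the true power without that label. No entry pattern or hazard shape tried reached 80% at 216 per group, although a hazard rising steeply over time (Weibull shape 1.5) comes close at 79%.

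**The analysis date is not fixed.** December 2032 might be read as a binding calendar cut. The text only anticipates it, and the end of study is tied to the last participant's radiotherapy. Nor is a missing event target a defect by itself, since an article may leave it to the full protocol or analysis plan. The finding rests on the stated number, inputs and power disagreeing with each other.

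**Conclusion.** The concern holds for the figure as written. The stated inputs require 111 to 116 IDFS events and about 266–279 evaluable patients per group, so 216 is 19–23% too few (216/266 = 0.81; 216/279 = 0.77). At 216 per group the expected yield is about 90 events and the power 69–71%. This is conditional on exponential IDFS and uniform entry; the shortfall persists, at varying size, under the departures tried.

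For the 540 to be enrolled, the consequence is smaller: about 80% power with no dropout and about 74–78% with 20% lost at a constant rate over 5 to 15 years. The 270 per group is roughly what the stated design needs before any loss, so the dropout allowance no longer protects against dropout.

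**What to change.** Retrieve the PASS inputs and correct the Sample size estimation section so that alpha, follow-up, number and power agree. State:
- the required events (111–116, naming the method);
- the expected events under the planned entry and follow-up;
- the resulting power with its survival, entry and dropout assumptions: about 70% for 216 evaluable per group, and about 74–78% for 540 enrolled with 20% loss.

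Optionally, to keep 80% power without more patients, time the primary analysis at the required number of IDFS events and not before 5 years after last entry. With 540 enrolled and 20% lost over 15 to 5 years, 111 events are expected about 5.4 to 6.7 years after last entry, and 116 about 5.8 to 7.3 years. This is one design choice among several; a larger sample or an openly lower power would also make the section consistent.

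The cost is amendment wording plus either a less favourable stated power or a later readout, within long-term follow-up that the article already foresees. The change is best made before any comparative results are seen, since the Data Safety Committee is to look at outcomes when half the subjects are enrolled and may vote on changing the plan.

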### Statistical analysis

Descriptive statistical analyses will be conducted based on demographic characteristics such as age, gender, height, weight and other baseline characteristics such as medical history. The Cox proportional hazards model will be used for analysis of the primary endpoint. The HR and its 95% CI will be calculated, including stratification factors and other covariates. Additionally, the Cox proportional hazards model without covariates will be used to support the analysis results of the primary endpoint. Moreover, the Kaplan-Meier (KM) method will be used to calculate the median IDFS for the two groups (experimental group vs control group), including 95% CIs. KM plots will be used to illustrate the time trends of IDFS. For the secondary endpoints, the AFR of each group will be calculated, as well as the corresponding 95% Clopper-Pearson CIs. LRFS, DMFS, RFS, OS, DFS and BCSM will be analysed for median values using the KM method (including 95% CIs). The overall changes in EORTC QLQ-C30 and EORTC QLQ-BS23 scores from baseline will be summarised. Safety analysis will be conducted by summarising AEs, changes in laboratory test results, changes in vital signs and study treatment exposure. The results will be reported by treatment group. All AEs during treatment, grade 3 or higher treatment-emergent AEs (TEAEs), SAEs, radiotherapy-related SAEs and TEAEs leading to study termination will be summarised by organ system, preferred term, and group in terms of numbers and percentages (see online supplemental file 16 for details). A p value of ≤0.05 in a two-tailed test will be considered statistically significant. Statistical analyses will be performed using SPSS V.25.0 and STATA V.14.

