### Objectives and endpoints

This study aims to evaluate whether adjuvant radiotherapy to the regional lymph nodes after BCS or chest wall plus regional lymph node radiotherapy after total mastectomy can further improve clinical outcomes in N1 patients with low clinical risk but high RecurIndex-LRR risk.

The primary endpoint is invasive disease-free survival (IDFS). Secondary endpoints are AFR, LRR-free survival (LRFS), DMFS, RFS, OS, DFS, BCSM and patient quality of life assessment. The specific definitions can be found in table 1.

**Table 1 T1:** The specific definitions of the study endpoints

IDFS	The time from the day the subject is randomised to the earliest occurrence of invasive cancer local recurrence, distant metastasis or death, but does not include contralateral breast second primary cancer.
AFR	Any ipsilateral chest wall, breast, regional lymph node recurrence or distant metastasis event that occurs during the follow-up period.
LRFS	The time from the day the subject is randomised to the earliest occurrence of ipsilateral chest wall, breast, or regional lymph node recurrence or death.
DMFS	The time from the day the subject is randomised to the earliest occurrence of distant metastasis or death.
RFS	The time from the day the subject is randomised to the earliest occurrence of ipsilateral chest wall, breast, regional lymph node recurrence, distant metastasis or death.
OS	The time from the day the subject is randomised until the patient’s death.
DFS	The time from the day the subject is randomised to the recurrence of the disease or the patient’s death due to disease progression.
BCSM	The time from the day the subject is randomised to death from breast cancer.

AFRany first recurrenceBCSMbreast cancer-specific mortalityDFSdisease-free survivalDMFSdistant metastasis-free survivalIDFSinvasive disease-free survivalLRFSlocal–regional recurrence-free survivalOSoverall survivalRFSrecurrence-free survival

During the screening period and 3 months after the end of treatment, patients in each group fill out the quality of life questionnaire (EORTC Core Quality of Life Questionnaire (EORTC QLQ-C30)), as well as the breast cancer survival quality scale (EORTC Breast Cancer-Specific Quality of Life Questionnaire (EORTC QLQ-BS23)) annually during the follow-up phase (onlinesupplemental files 2  3).

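### Any first recurrence (AFR) is planned as a crude proportion over unequal follow-up with no time horizon, and the DFS definition leaves out deaths that the sister endpoints count

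*Protocol article*

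**What the plan says.** All places are in the Protocol article.

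- **AFR, definition** (Objectives and endpoints, Table 1): "Any ipsilateral chest wall, breast, regional lymph node recurrence or distant metastasis event that occurs during the follow-up period". It has no time origin and no fixed time point, unlike every other entry in the table.
- **AFR, analysis** (Statistical analysis): "the AFR of each group will be calculated, as well as the corresponding 95% Clopper-Pearson CIs".
- **DFS, definition** (Table 1): time from randomisation "to the recurrence of the disease or the patient’s death due to disease progression". In the same table IDFS runs to the "earliest occurrence of invasive cancer local recurrence, distant metastasis or death", and RFS, LRFS and DMFS likewise count death without limit on cause.
- **BCSM, definition** (Table 1): "The time from the day the subject is randomised to death from breast cancer".
- **DFS and BCSM, analysis** (Statistical analysis): "LRFS, DMFS, RFS, OS, DFS and BCSM will be analysed for median values using the KM method (including 95% CIs". No competing-risk method is named.
- **Follow-up:** enrolment is expected to last 5 years (Participants and recruitment). The end-of-study visit falls 60 months after the last participant's radiotherapy (Follow-up evaluation and toxicity assessment). Sample size estimation allows 20% dropout, mainly with 10- and 15-year follow-up in mind.

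**The concern.** A Clopper-Pearson interval is an exact binomial interval. It treats each patient as fully observed over the same period. Here an early enrollee has about 10 years in which to recur, a late enrollee about 5, and a patient who drops out fewer still. All count equally in the denominator, and anyone censored counts as recurrence-free. The result depends on the enrolment pattern and the loss to follow-up as well as on recurrence. It cannot be set beside 5- or 10-year rates from other trials.

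AFR may also carry more weight than its place in the list suggests. The other time-to-event secondary endpoints are to be summarised by Kaplan-Meier medians. On the plan's own rates, control IDFS would still be 0.82² = 67% at 10 years, so such medians are unlikely to be reached.

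DFS raises a question of definition. A patient who dies of another cause without recurrence is an event for IDFS, RFS, LRFS and DMFS but not for DFS. A reader would not expect that from the name, and Table 1 does not say how such deaths are treated. Under Kaplan-Meier, censoring is the natural reading. For BCSM the same censoring makes one minus Kaplan-Meier too high if it is read as the risk of dying of breast cancer.

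**Working it through.** **Inputs.** The document gives no rate for AFR, BCSM or other-cause death. For AFR I borrow the 5-year IDFS of 82% (control) and 89% (experimental) from Sample size estimation. IDFS includes deaths, so this is an illustration and not a forecast. I assume constant hazards, uniform entry over 5 years and 5 further years of follow-up. As a check on the inputs, ln(0.89)/ln(0.82) = 0.587, the hazard ratio that the plan states.

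**AFR.** The hazards are L = −ln(0.82)/5 = 0.0397 per year (control) and −ln(0.89)/5 = 0.0233 (experimental).

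With dropout hazard m and a = L + m, the expected crude proportion is

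L/a × [1 − (e^(−5a) − e^(−10a))/(5a)].

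- Control, no dropout: 1 − (0.82 − 0.6724)/(5 × 0.0397) = 25.6%.
- Control, 20% lost by year 5: m = −ln(0.8)/5 = 0.0446 and a = 0.0843, so 0.4707 × (1 − 0.5353) = 21.9%.

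| | 5-year risk | 10-year risk | Crude, no dropout | Crude, 20% lost by year 5 |
|---|---|---|---|---|
| Control | 18.0% | 32.8% | 25.6% | 21.9% |
| Experimental | 11.0% | 20.8% | 16.0% | 13.6% |

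In every row the crude figure lies between the two risks and equals neither.

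**AFR between arms.** Randomisation balances staggered entry. With equal dropout the ratio of arms hardly moves: 16.0/25.6 = 0.625 and 13.6/21.9 = 0.621. A difference where the recurrence hazards are equal requires unequal dropout. If 10% were lost in one arm and 20% in the other by year 5, the crude figures at the control hazard would be 23.7% and 21.9%, a gap of 1.9 points before rounding. At the experimental hazard they would be 14.8% and 13.6%, a gap of 1.2 points. These dropout rates are assumed.

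**DFS.** Table 1 shows the inconsistency without arithmetic. To give it a scale, assume other-cause mortality o = 0.8% per year and use the IDFS hazards for recurrence. Deaths without prior recurrence by year 5 are o/(o + L) × [1 − e^(−5(o + L))], or 3.6% (control) and 3.7% (experimental). The two arms are nearly equal because o was set equal.

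**BCSM.** With breast-cancer death hazard b and other-cause hazard o, one minus Kaplan-Meier is 1 − e^(−bt), and the true cumulative incidence is b/(b + o) × [1 − e^(−(b + o)t)]. Both sets of rates are assumed.

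| b, o per year | Year | 1 − KM | Cumulative incidence | Excess (points) |
|---|---|---|---|---|
| 1.2%, 0.8% | 5 | 5.8% | 5.7% | 0.1 |
| 1.2%, 0.8% | 10 | 11.3% | 10.9% | 0.4 |
| 2.0%, 1.0% | 5 | 9.5% | 9.3% | 0.2 |
| 2.0%, 1.0% | 10 | 18.1% | 17.3% | 0.8 |

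**The case against.** The strongest reply concerns reach, and most of it stands.

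- **Dropout.** The 20% allowance is explained mainly by follow-up beyond the 5-year endpoint, so 20% lost by year 5 is a pessimistic reading. That weakens the 21.9% figure. It leaves the 25.6% figure, which assumes no dropout, and the missing time horizon untouched.
- **Bias between arms.** A reader might infer that the AFR comparison is biased because the trial is open-label. The document gives no loss by arm and sets 6-monthly checks for patients with and without radiotherapy. Even the assumed gap of 1.9 points is about half the standard error of a two-arm difference: √(2 × 0.22 × 0.78/270) = 3.6 points.
- **DFS tilt.** A reader might infer that leaving out non-cancer deaths favours regional nodal irradiation, since ischaemic heart disease and pneumonitis are among the listed toxicities. That would need more such deaths in the irradiated arm, and nothing in the document shows this. Deaths of any cause are also counted in IDFS, RFS, LRFS, DMFS and OS.
- **BCSM.** The plan names Kaplan-Meier for medians and does not say that its complement will be read as mortality risk. Censoring other deaths is correct for a cause-specific hazard ratio. The excess is small.
- **A widened DFS might duplicate RFS.** This is fair, and the fix has to deal with it.

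The reply does not reach the central point. The article itself states the AFR method and the DFS wording, so neither is a detail left to an unseen analysis plan.

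**Conclusion.** The point holds for secondary endpoints only. The primary IDFS endpoint counts death from any cause and is analysed by a Cox model.

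- **AFR** is the material part. As planned, it has no time horizon and treats censored patients as recurrence-free. On borrowed IDFS rates the control figure would be about 22% to 26%, where the 5-year risk is 18.0% and the 10-year risk is 32.8%. This rests on constant hazards, uniform entry and the borrowed rate. Bias between arms would arise only if dropout differed by arm, which is an assumption.
- **DFS** is inconsistent with the other composite endpoints in Table 1. No direction of effect is shown.
- **BCSM** is minor: about 0.1 to 0.2 points at 5 years and 0.4 to 0.8 points at 10 years, under assumed death rates.

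**What to change.** 1. **AFR:** define it as time from randomisation to first recurrence. Report Aalen-Johansen cumulative incidence at 5 years, and at 10 years where follow-up supports it, with 95% CIs and death without recurrence as a competing event. Add a cause-specific hazard ratio. Drop the Clopper-Pearson proportion.
2. **DFS:** either replace "death due to disease progression" by death from any cause and state how DFS then differs from RFS, or keep the restriction, rename the endpoint and treat other deaths as competing events.
3. **BCSM:** report cumulative incidence with other-cause death as a competing event, plus a cause-specific hazard ratio.

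The cost is wording in Table 1 and the Statistical analysis section, and the loss of a simple AFR proportion. No extra patients or visits are needed, cause of death is already required for BCSM, and Stata, which the plan names, can do the analyses. Final primary-outcome data are expected by December 2032, so there is time to settle this before analysis.

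### Kaplan-Meier medians are the only analysis the article states for six secondary endpoints, and on its own planning rates they will almost certainly not be reached

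*Protocol article*

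**What the plan says.** All references are to the protocol article.

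- **Statistical analysis, secondary endpoints:** "LRFS, DMFS, RFS, OS, DFS and BCSM will be analysed for median values using the KM method", with 95% CIs. The section states no hazard ratio, test or fixed-time rate for these six endpoints. AFR is handled separately, as a proportion per group with an exact interval.
- **Statistical analysis, primary endpoint:** a Cox model gives the IDFS hazard ratio with 95% CI, including stratification factors and other covariates. A Cox model without covariates supports it. In addition, "the Kaplan-Meier (KM) method will be used to calculate the median IDFS for the two groups", and Kaplan-Meier plots are planned.
- **Sample size estimation:** 5-year IDFS "in the experimental group and control group in this study will be 89% and 82%, respectively". The target is to "improve the primary endpoint IDFS by ≥7% (HR=0.587").
- **Participants and recruitment:** registration starts on 1 April 2023, and primary outcome data are complete by December 2032.

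**The concern.** A Kaplan-Meier median exists only if the estimated curve falls to 50%. The plan expects more than 80% of patients in each group to be free of an IDFS event at 5 years, and follow-up stops before year 10. For endpoints with no more events than IDFS, a median is the wrong summary.

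The six secondary endpoints carry much of the clinical argument. The Discussion explains the choice of IDFS by the effect of radiotherapy on local-regional recurrence and distant spread, which LRFS and DMFS measure directly. Followed literally, the stated analysis would give not reached in both groups for these endpoints, with no treatment comparison. A comparison chosen later would be chosen with data in hand, in an open-label trial. The 5-year rate around which the trial was sized is also not among the numerical summaries named for IDFS.

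**Working it through.** **Inputs.** Sample size estimation: 5-year IDFS 82% (control) and 89% (experimental); HR 0.587; 5-year enrolment and 5-year follow-up; 216 per group before and 270 after a 20% dropout allowance. Participants and recruitment: April 2023 to December 2032, so at most about 9.7 years for the first patient enrolled. Assumption: exponential survival.

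**1. The plan's own figures.** HR = ln(0.89)/ln(0.82) = 0.1165/0.1985 = 0.587, as stated. The dropout step also reproduces: 216/(1 − 0.20) = 270. The exponential assumption is therefore consistent with the stated effect.

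**2. Implied medians.** Median = 5 × ln 2 / (−ln S5), where S5 is the 5-year rate.
- Control: 5 × 0.6931/0.1985 = 17.5 years.
- Experimental: 5 × 0.6931/0.1165 = 29.7 years.

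**3. Where the curves stand.** S(t) = S5^(t/5).

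| Time | Control | Experimental |
|---|---|---|
| 10 years | 0.82² = 67.2% | 0.89² = 79.2% |
| 15 years | 0.82³ = 55.1% | 0.89³ = 70.5% |

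A median within 10 years needs S5 ≤ √0.5 = 70.7%. For 9.75 years it needs 0.5^(5/9.75) = 70.1%.

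**4. Chance of reaching 50%.** Each scenario was simulated 10,000 times, with 216 or 270 per group, uniform 5-year accrual, administrative censoring between 5 and 10 years, and with or without dropout.

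| IDFS, design rates | Curve reaches 50% | Lower 95% limit of median estimable |
|---|---|---|
| Control | 1.1–1.6% | 11–17% |
| Experimental | 0.1–0.3% | 2–4% |

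Where the curve does reach 50%, it does so in the sparse tail.

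**5. Secondary endpoints.** By Table 1, LRFS, DMFS, OS, DFS and BCSM count broadly a subset of the IDFS events, and RFS nearly the same events. Their medians therefore lie at or beyond those of IDFS.

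**6. Sensitivity to the other cited rates.**

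| Cited 5-year IDFS | Implied median |
|---|---|
| MA20 control, 81.9% | 17.4 years |
| EORTC 22922 control, 77.1% | 13.3 years |
| Retrospective RecurIndex study, radiotherapy, 81.1% | 16.5 years |
| Retrospective RecurIndex study, control, 69.7% | 9.6 years |

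Only the last comes within follow-up. The simulated control curve then reaches 50% in about 53–56% of trials.

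**7. What can be estimated.** With accrual A = 5 and further follow-up F = 5, the event probability is 1 − [exp(−λF) − exp(−λ(A+F))]/(λA), where λ = −ln(S5)/5.
- Control: 1 − (0.82 − 0.6724)/0.1985 = 0.256, so 270 × 0.256 ≈ 69 events.
- Experimental: 1 − (0.89 − 0.7921)/0.1165 = 0.160, so 270 × 0.160 ≈ 43 events.

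About 112 IDFS events in total, with no loss to follow-up, are enough for hazard ratios and fixed-time rates.

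**The case against.** **The primary analysis is intact.** A reader might infer that the IDFS result is compromised. It is not. The Cox hazard ratio is the primary analysis and estimates the effect on which the trial was sized. The Kaplan-Meier plots will show the curves at 5 years, and the median is an addition. This stands, and it confines the harm for IDFS to an uninformative extra summary.

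**The article is a condensation.** A reader might infer that the trial has no planned comparison for the secondary endpoints. The document does not support that. The section points to supplemental file 16 (after the safety summaries), which is not shown, and a separate analysis plan may exist. One can say only that the article states no comparison. The point does not rest on silence, though: the text names an estimator, and that estimator is unsuitable.

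**Never reached is too strong.** This also stands. Under the design rates the chance is about 1% in the control arm. Under the retrospective control rate it is about even for that arm. That study is the only cited source on high RecurIndex-LRR risk patients. However, its radiotherapy arm still has a median of 16.5 years, so the two medians still could not be compared.

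**Follow-up may be longer.** Sample size estimation mentions later follow-up to 10 and 15 years. At 15 years the expected IDFS is still 55% and 70.5%, so this does not rescue the medians.

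**Kaplan-Meier gives the whole curve.** Fixed-time rates can indeed be read from it without new data. That makes the repair cheap, but it does not make the median the right quantity to name.

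**Conclusion.** The point holds in a limited form. The article names a summary for six secondary endpoints that, on its own planning rates, will almost certainly be not reached in both arms. The IDFS medians are about 17.5 and 29.7 years, against at most about 9.7 years of follow-up at the primary cut-off.

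This rests on exponential survival, on the 82% and 89% planning rates, and on the secondary endpoints having broadly no more events than IDFS. The overlap of events is approximate, because the Table 1 definitions do not nest perfectly. Only a control arm as poor as the retrospective 69.7% would bring one median to the edge of follow-up.

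It should be fixed before analysis. It does not threaten the primary endpoint, the sample size or the main conclusion.

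**What to change.** Amend the Statistical analysis section as follows.

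- **IDFS, LRFS, DMFS, RFS, OS and DFS:** replace the medians with Kaplan-Meier 5-year (later 10-year) rates per group and the between-group difference, each with a 95% CI.
- **Each secondary time-to-event endpoint:** report a hazard ratio with 95% CI from the Cox model with stratification factors already planned for IDFS.
- **BCSM:** report cumulative incidence with death from other causes as a competing event, plus a cause-specific hazard ratio. One minus Kaplan-Meier would overstate cumulative breast cancer mortality.

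If the full protocol or analysis plan already specifies these, align the article's text with it.

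The cost is wording only, with no new data and no change to the sample size. Enrolment is planned to run until January 2028, so the change can be made well before the analysis.
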